# Study protocol: HipSTHeR - a register-based randomised controlled trial – hip screws or (total) hip replacement for undisplaced femoral neck fractures in older patients

**DOI:** 10.1186/s12877-020-1418-2

**Published:** 2020-01-21

**Keywords:** Hip fracture, Femoral neck fracture, Internal fixation, Hip arthroplasty, Register, Register-based randomised controlled trial

## Abstract

**Background:**

Femoral neck fractures (FNFs), which are common in the older population, are associated with high mortality and morbidity. Some 20% of FNFs are undisplaced (uFNFs). The routine surgical procedure for uFNFs is internal fixation (IF) with 2–3 screws/pins with a reported reoperation rate in older patients (age ≥ 75 years) of up to 21%. The reoperation rate for hemiarthroplasties for displaced fractures is lower than for undisplaced fractures operated with IF. This study will aim to determine whether the outcome for older patients with an uFNF can be improved by replacing the hip instead of preserving it.

**Methods:**

A national multicentre, register-based, randomised controlled trial (rRCT) will be conducted. For this trial, 1440 patients, ≥75 years with an acute uFNF, will be allocated. Eligible patients will be identified by the Swedish Fracture Register (SFR) platform, which will notify the admitting orthopaedic surgeon of eligibility. After informed consent has been given and documented, patients will be randomised to either IF (control group) or arthroplasty (intervention group) within the SFR platform. Injury mechanism, fracture classification, date of injury, and type of treatment are registered in the SFR. Type and brand of arthroplasty, surgical approach, and fixation are obtained from the Swedish Hip Arthroplasty Register (SHAR). The study cohort from the SFR will be cross-checked with the National Patient Register and the SHAR for outcome variables at 2, 5, and 10 years.

The primary outcome will be a composite variable comprising reoperation rate and mortality at 2 years postoperatively. Secondary endpoints will include reoperation rate and mortality as stand-alone variables. In addition, secondary endpoints will be patient-reported outcomes as measured by the Short Musculoskeletal Functional Assessment questionnaire at 1 year postoperatively as routinely collected within the SFR. Further secondary endpoints will include the occurrence of adverse events such as pneumonia, stroke or myocardial infarction and evaluation of the external validity of the study.

**Discussion:**

This large, multicentre, register-based randomised controlled trial could potentially shift the treatment of uFNFs in older patients towards primary hip arthroplasty in order to improve the outcome.

**Trial registration:**

The trial is registered at www.clinicaltrials.gov (NCT03966716); May 29, 2019.

## Background

Hip fractures are a major cause of injury, morbidity and death in older patients. Undisplaced FNF (uFNF) are classified according to the Garden classification system on the anteroposterior X-ray [1, 2]. The routine surgical procedure for uFNFs, regardless of the patient’s age, is internal fixation (IF) with 2–3 screws or pins. Advanced age has been described as a risk factor for healing complications in uFNFs [3, 4]. In older patients reoperation rates ranging between 8 and 21% have been reported in the literature [2, 5–7]. In older patients displaced FNFs are treated with hip arthroplasty, which produces better and more predictable results compared with IF [5]. The reoperation rate for hemiarthroplasties for displaced FNFs is lower than for undisplaced fractures that are operated with IF [5, 8, 9]. A randomised controlled trial (RCT) comparing modern hemiarthroplasty with screw fixation for uFNFs found no significant difference in hip function but hemiarthroplasty led to improved mobility and fewer major reoperations [8].

In the Swedish Fracture Register (SFR) all fracture types in adults and all long-bone fractures in children are registered [10]. The SFR is a unique national quality register as it contains information on fractures, regardless of treatment (surgical or non-surgical). Seventy-five per cent of the hospitals in Sweden that manage fractures on a regular basis participate in the SFR.

A question often arises as to whether the results from an RCT can be extrapolated from the study environment to a general health care setting [11, 12]. Active participation of patients and recruitment of large sample sizes in an RCT are not easily achieved and refusal to participate and loss to follow-up (a form of selection bias) are prevalent problems. Conducting register-based RCTs (rRCTs), which include a randomisation module in a large, all-inclusive clinical register with unselected consecutive enrolment, can combine some of the most important features of a prospective randomised trial with the inclusiveness and efficiency of a large-scale clinical register. The consecutive enrolment in combination with patient identification and automated linked register-based follow-up allows for a cost-effective model with analysis of those who are lost to follow-up [13].

There are limited data comparing IF and hip arthroplasty for uFNF fractures and trials have been called for to optimise the surgical treatment [2, 14].

### Aim

This study will aim to compare IF and hip arthroplasty for uFNF in the older patient using a composite variable consisting of reoperation rate and mortality. Patient-reported outcome measures (PROMs) and the frequency of adverse events will also be assessed.

## Methods/design

### Trial design, settings, and location

Hipsther is a multicentre, register-based, RCT of 1440 older patients who have sustained an uFNF. The study will be carried out from 2019 to 2029 (inclusion period 2019–2022). Patients ≥75 years with an uFNF will be identified by the registration platform. The admitting orthopaedic surgeon at a participating hospital will receive an alert about the eligibility of the patient. After screening has been performed and patient consent obtained, randomisation to either IF or arthroplasty will be carried out within the platform of the SFR before surgery. The guidelines of Good Clinical Practice (GCP-ICH) will be followed. The trial is initiated, designed, and performed as an academic investigation and registered at ClinicalTrials.gov (NCT03966716). The trial will follow the guidelines of the CONSORT (Consolidated Standards of Reporting Trials) Statement.

### Study subjects and eligibility criteria

All patients with a nondisplaced (Garden 1–2) FNF who are admitted to the participating hospitals will be screened for participation in the study. Screening will be performed during the registration in the SFR before surgery after admission to the hospital. The inclusion criteria are an acute (within 72 h) undisplaced or minimally displaced FNF (Garden 1–2) [1], age ≥ 75 years, eligible for IF or hip arthroplasty, and obtained written informed consent. Patients with dementia can be included after consent from a next of kin or power of attorney. Patients with stress or with pathological and peri-implant FNFs are excluded. In the event of bilateral uFNF during the study period only the first hip will be included and randomised.

### Randomisation and blinding

Randomisation will be computer generated and part of the research platform in the SFR. Patients are identified as eligible in conjunction with registration of demographic data and fracture pattern. In participating hospitals, the platform will alert the admitting orthopaedic surgeon about the possibility to include the patient in the study. The inclusion criteria will be stated (uFNF, ≥75 years, and fracture < 3 days old) and the treating surgeon will be asked whether the patient is eligible for inclusion and whether consent has been obtained. After screening and inclusion, the patient will be randomised within the SFR platform to receive either IF (with 2–3 screws or pins) or arthroplasty. The randomisation procedure has to be done before the patient is taken to the surgical theatre to prepare for the elected procedure. There will be no blinding given to treatment assignment. The steering committee will have no access to treatment comparisons in accumulated data until the database is locked.

### Surgical intervention

#### Hip Arthroplasty

Hip arthroplasty (hemi- or total) is performed according to the present routine at the participating hospitals. Patients > 80 years of age, cognitive dysfunction, low demand or short remaining life expectancy are normally managed with hemiarthroplasty. Patients between 60 and 79 years of age, high level of activity, and osteoarthritis or rheumatoid arthritis of the fractured hip are routinely managed with total hip arthroplasty (THA). The final decision of whether to perform a hemiarthroplasty or THA is ultimately determined by the treating surgeon. Type and brand of arthroplasty, surgical approach and method of fixation are based on the preferences of the treating surgeon and department.

#### Internal fixation

IF will be carried out with the patient on a fracture table and with the aid of an image intensifier using two cannulated screws/pins or a conventional sliding hip device. Thromboprophylaxis and antibiotic prophylaxis will be administered to patients as per hospital routine.

### When and how to withdraw patients from the trials

Should a patient request or decide to withdraw from the study, all efforts will be made to complete and report the observations as thoroughly as possible up to the point of withdrawal. For those patients who withdrew, the last post-baseline observation will be carried forward. In a case of withdrawal of full consent, the patient will be followed according to the routine standard follow-up of patients at the responsible institution but excluded from further analysis.

### Outcome measurements

#### Primary endpoint

The primary outcome of this rRCT will be a composite variable (reoperation rate and mortality). Arthroplasty is a more elaborate surgical procedure that might affect peri- and postoperative short-term mortality, as related to longer operating times, higher blood loss, and the occurrence of bone cement implantation syndrome. A higher mortality in one study group would affect the reoperation rate in that group. Therefore, we decided to construct a composite variable as the primary outcome. There will be no formal follow-ups in addition to the local clinical routines. Data on mortality and reoperations are registered in the National Patient Register (NPR) (all codes for procedures and diagnoses from hospitals), the Swedish Hip Arthroplasty Register (SHAR) (change of implant, reoperation due to dislocation, fracture or infection) and in the SFR (fracture close to implant, removal of pins/screws, conversion to arthroplasty).

#### Secondary endpoints

Secondary endpoints will include reoperation rate and mortality as stand-alone variables.

PROM, as measured by the Short Musculoskeletal Functional Assessment (SMFA) questionnaire [15], will be routinely collected within the SFR 1 year after the injury and compared with the results obtained by recall technique at the time of the fracture. No additional PROMs will be collected.

Other secondary endpoints will include the occurrence of adverse events defined as suffering, physical harm or disease, as well as death related to the index admission and as a condition that was not an inevitable consequence of the patient’s disease or treatment. The external validity of the trial will be evaluated by comparing the outcome between those who were included in the rRCT with those who fulfilled the inclusion criteria but declined to participate.

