### Estimated sample size and power

The reoperation rate for hemiarthroplasty due to FNF is estimated at 5% according to reports from the SHAR [16, 17]. In recent registry based studies, patients with an FNF treated with THA had a significantly reduced risk of reoperation when compared with patients treated with hemiarthroplasty [18, 19]. Because we know that the variable “reoperations” does not have 100% completeness in the SHAR given that some procedures (e.g., debridement and irrigation or closed reduction) are not reliably registered, we assume that the actual reoperation rate is closer to 7.5%. The reported reoperation rates for uFNFs vary [6, 7, 20, 21], but we estimate that the rate is about 12.5% at 1 year after IF with screws/pins in older patients with uFNF. Mortality rates are reported from 11% at 1 year in a study with both displaced and undisplaced FNFs [22] to just over 20% in other studies [6, 8, 21].

In our primary outcome composite variable (reoperation rate and mortality), we expect a 15% 1-year mortality within the study cohort. We assume that death or reoperation would occur within 1 year in 27.5% (15% + 12.5%) of the patients in the control group (IF) and aim to detect a decrease to 22.5% (15% + 7.5%) in the intervention group (arthroplasty). We plan to include patients for 3 years. Patients will be censored at the time of reoperation or at time of death within 2 years, at time of withdrawal of informed consent or at the end of the study. The end of study will be when the last patient has a 1-year follow-up, cross-checking with the NPR has a 1 year delay for data completeness; hence, about two thirds of the patients will have a 2-year follow-up and the remaining patients between 1 and 2 years. Simulations under an assumption of constant hazard indicate that 1440 patients enrolled for 3 years, yielding about 586 events, would produce a power of 80% to detect such a difference. The analyses were performed using R v. 3.3.1 and the survival package v. 2.39.4.

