## Discussion

The present trial will provide improved evidence for the future choice of treatment for patients with Garden 1–2 FNF who are ≥75 years old.

Patients with dementia represent a large proportion of the hip fracture population but the inclusion of this group is difficult because of the need of informed consent by next of kin (or power of attorney) and thus exposes the study for inclusion bias. Informed consent has been constructed in two versions, one for lucid patients and one for patients with cognitive impairment not able to give informed consent; the latter version allows us to address next of kin. There is a national effort in Sweden to treat hip fractures within 24 h of admission and with operative intervention performed only during duty hours, the recruitment process is difficult, which could result in selection bias. The Garden classification does not take into account posterior or anterior fracture tilt. There are reports discussing the linkage of posterior and anterior tilt to failure after IF, a situation that might lead to reluctance to include these patients in this study [20, 21, 23–25].

The primary endpoint, defined as a composite variable (reoperation rate and mortality), is constructed to consider both mortality and reoperations. A longer and more strenuous initial procedure (i.e. arthroplasty) might affect peri- and postoperative mortality and thus mask potential reoperations. However, a recent RCT comparing hemiarthroplasty and IF in patients with uFNF reported a higher mortality rate after IF [8].

The external validity of the trial will be evaluated by comparing mortality, complications, and PROM between those who were included in the rRCT, those who fulfil the inclusion criteria for the rRCT trial but declined participation, and those eligible but not screened. The limitations of the present trial include the lack of blinding of surgeons and patients, the potential of randomisation bias because the two compared procedures (IF, arthroplasty) differ in complexity, required surgeon skills, and duration. The strengths of the study are the pragmatic rRCT study design that includes a national coverage of hospitals, a large sample size, and clinically relevant outcomes. The results from the study will be dispersed to the medical community by way of presentations and publications in relevant medical journals.

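### The external-validity comparison sets a mixed IF and arthroplasty trial population against non-participants for whom IF is routine, so any treatment-dependent outcome mixes selection with treatment effect

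*Protocol article*

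**What the plan says.** External validity is listed among the secondary outcomes in the Abstract and in the note to Table 1. The section Secondary endpoints defines the evaluation as "comparing the outcome between those who were included in the rRCT with those who fulfilled the inclusion criteria but declined to participate". The Discussion returns to it: "The external validity of the trial will be evaluated by comparing mortality, complications, and PROM between those who were included in the rRCT", with two further groups, those who met the criteria "but declined participation, and those eligible but not screened". Neither section restricts the comparison to one trial arm or refers to treatment received.

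On treatment inside the trial, the section Randomisation and blinding says that "the patient will be randomised within the SFR platform to receive either IF (with 2–3 screws or pins) or arthroplasty". On treatment outside it, the Background says: "The routine surgical procedure for uFNFs, regardless of the patient’s age, is internal fixation (IF"), and the Abstract says the same.

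The section Estimated sample size and power plans for a 1-year composite of 27.5% with IF and 22.5% with arthroplasty. Both figures contain the same 15% mortality; reoperation is 12.5% and 7.5%.

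**The concern.** External validity asks whether the patients who entered the trial resemble those who could have entered but did not. An outcome comparison answers that only if the two groups were treated alike, or if treatment is taken into account. Here the groups differ in treatment by design. If arthroplasty lowers reoperation as hypothesised, participants as a whole will show fewer events than non-participants of identical prognosis, and this could be read as selection of healthier patients. Conversely, if participants are at higher risk, the benefit in the arthroplasty arm can offset it and hide real selection.

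The Discussion itself expects possible inclusion or selection bias, from consent by next of kin, from the pressure to operate within 24 hours and from reluctance to include tilted fractures. This endpoint is the planned check on such bias, so its contrast should isolate selection as far as the data allow.

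**Working it through.** **Inputs.** From Estimated sample size and power: 1-year composite 27.5% (IF) and 22.5% (arthroplasty), reoperation 12.5% and 7.5%, mortality 15% in both arms, 1440 patients, about 586 events, 80% power, 3 years of accrual, follow-up of 1 to 2 years. Assumptions, because the article does not state them: 1:1 allocation, two-sided 5% level, and x, the share of non-participants receiving arthroplasty.

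**The plan's own figure.** Constant hazards: −ln(0.725) = 0.3216 and −ln(0.775) = 0.2549, hazard ratio 0.793. With uniform accrual over 3 years, study end at year 4 and censoring at 2 years, the probability of an observed event is 0.4429 (IF) and 0.3715 (arthroplasty). Expected events are 720 × (0.4429 + 0.3715) ≈ 586. The Schoenfeld formula with 586 events gives 80.3% power, and a log-rank simulation of 4000 runs gives 80.4%. The stated design reproduces, which is consistent with 1:1 allocation.

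**Gap with no selection at all.** Non-participants are given the same prognosis as participants.

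- Trial, both arms, 1-year composite: (27.5 + 22.5)/2 = 25.0%. Non-participants: 27.5 − 5x. Gap: 2.5 − 5x = 5 × (0.5 − x) points.
- Trial, both arms, 1-year reoperation: (12.5 + 7.5)/2 = 10.0%. Non-participants: 12.5 − 5x. The gap is the same.
- 2-year composite: 1 − 0.725² = 47.44% and 1 − 0.775² = 39.94%. Trial mean 43.69%. Gap: 7.5 × (0.5 − x) points.
- 1-year mortality: 15% against 15%. Gap 0.

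| x | 1-year composite or reoperation gap (points) | 2-year composite gap (points) |
|---|---|---|
| 0 | 2.5 | 3.75 |
| 0.10 | 2.0 | 3.0 |
| 0.25 | 1.25 | 1.9 |
| 0.50 | 0 | 0 |

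**Sensitivity to allocation.** If a share s of the trial receives arthroplasty, the 1-year gap is 5 × (s − x). With x = 0 this is 1.7 points at s = 1/3 and 3.3 points at s = 2/3.

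**Masking.** Suppose all non-participants receive IF and their true 1-year risk under IF is 25.0%, which is 2.5 points below the trial IF arm. The comparison is then 25.0% against 25.0%, and a real difference in risk does not show.

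**Chance of a misleading result.** The article attaches no test to this endpoint, so this is only an illustration, with assumed numbers of non-participants. With equal prognosis, the chance that a two-sided 5% test finds non-participants significantly worse at 1 year is:

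| Non-participants | Reoperation, x = 0 | Composite, x = 0 | Reoperation, x = 0.25 | Composite, x = 0.25 |
|---|---|---|---|---|
| 500 | 35% | 20% | 13% | 8% |
| 1000 | 49% | 28% | 17% | 10% |
| 1440 | 57% | 33% | 19% | 12% |

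The nominal value in that direction is 2.5%.

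**Within treatment.** At equal prognosis within treatment groups, the trial IF arm against IF-treated non-participants is 27.5% against 27.5%, an expected gap of 0.

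**The case against.** The article names the groups to be compared. It does not say that the arms will be pooled without regard to treatment, and an analysis plan could stratify. Type of treatment is recorded in the SFR, so the data allow it. This stands against a reading that the endpoint can never separate selection from treatment. It does not remove the point: the contrast described in both places is included against not included, and followed as written it confounds the two.

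The outcomes named in the Discussion are mortality, complications and PROM. Mortality carries no artefact on the planning rates, and the article gives no expected difference for PROM. The gaps above come entirely from reoperation. They apply if the outcome meant under Secondary endpoints is the composite or reoperation, or if complications include reoperation. This stands and limits the size of the claim.

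Both the 1:1 ratio and the treatment of non-participants are inferred. This also stands, and is why the result is given as a function of x and s.

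A within-treatment comparison is not perfectly clean either. Outside the trial, treatment is not randomised. The Discussion links fracture tilt to failure of IF; if such patients outside the trial tend to receive arthroplasty, IF-treated non-participants become a selected, lower-risk group. The fix has to say so.

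Finally, a reader might take the two groups under Secondary endpoints and the three in the Discussion as a contradiction. The longer list contains the shorter one, so this is a matter of alignment.

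**Conclusion.** The point holds for outcomes that depend on treatment. Under 1:1 allocation, equal prognosis and the planning rates, the comparison carries a spurious 1-year gap in reoperation and the composite of up to 2.5 points, half the 5-point effect the trial is designed to detect. The gap shrinks as more non-participants receive arthroplasty and vanishes when their share equals the trial's. The 2-year figure also rests on constant hazards. Mortality is unaffected under the planned equal rates; complications and PROM are affected only where the treatments differ.

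A reader might infer that the endpoint is bound to give a wrong answer whenever the trial is positive. The documents do not support that: the shift is modest, it depends on x and on the outcome chosen, and no decision rule is attached. Nor do they support any doubt about the randomised comparison, which does not use non-participants. This is a correction to one secondary endpoint.

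**What to change.** Rewrite the external-validity analysis in two parts.

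1. Compare baseline characteristics of all participants with those of all eligible non-participants, showing decliners and patients not screened separately. Treatment does not affect this comparison, and it addresses representativeness directly.
2. Compare outcomes within treatment received: chiefly the trial IF arm against IF-treated non-participants, again with decliners and patients not screened shown separately, and arthroplasty against arthroplasty where numbers allow. Adjust for age and other registered baseline factors.

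State that treatment outside the trial is not randomised, so residual selection may remain even within treatment. Use the same groups and the same named outcomes under Secondary endpoints and in the Discussion, and say whether reoperation is among them.

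The cost is wording and some precision; the register sources stay the same. For example, with an assumed 1000 IF-treated non-participants and a 27.5% rate, the standard error of the difference rises from √(0.275 × 0.725 × (1/1440 + 1/1000)) = 1.84 points to √(0.275 × 0.725 × (1/720 + 1/1000)) = 2.18 points.
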